### Research measures and valuables

The variables assessed at each time point in this study are summarized in Table 1.

**Table 1 Tab1:** Collection of data on exposures, outcomes, and other explanatory variables at each assessment point

Item	Time of admission (T1)	Time of discharge (T2)	6-month follow-up (T3)	12-month follow-up (T4)
Patient-reported outcomes/experiences				
Quality of life (EQ-5D-5L)	✓	✓	✓	✓
Perception of disabilities (SDS-J)	✓	✓	✓	✓
Empowerment and self-agency related scale	✓	✓	✓	✓
Satisfaction with care		✓	✓	
Subjective relationship with family		✓	✓	
Clinical and social variables				
Past hospitalisation or readmission				
Number of admissions^a^	✓	✓	✓	✓
Length of hospitalisation^a^	✓	✓	✓	✓
Type of hospitalisation (voluntary/involuntary)^a^	✓	✓	✓	✓
Reasons for emergency admission^a^	✓	✓	✓	✓
Unplanned discharge from index admission^a^		✓		
Psychiatric present status^b,c^	✓			
Symptoms (1 item)	✓	✓	✓	✓
Social relationships (1 item)	✓		✓	✓
Employment status	✓	✓	✓	✓
Functioning (PSP)	✓	✓	✓	✓
History of problematic behaviours^b^	✓	✓	✓	✓
Risk of problematic behaviours	✓	✓	✓	✓
Weight	✓	✓	✓	✓
Body mass index	✓	✓	✓	✓
Other exposure variables				
Socio-demographics				
Age^a^, sex, living condition, living location, social security etc.	✓			
Diagnostic information^a^				
Psychiatric disorders^a^	✓	✓		
Physical disorders^a^	✓	✓		
Past utilisation of services				
Emergency services^b^	✓			
Police or administrative interventions	✓			
Community medical services^b^	✓		✓	✓
Outpatient services^a,b^	✓		✓	✓
Social and welfare services^b^	✓		✓	✓
Case management or outreach services	✓	✓	✓	✓
Crisis planning^b^	✓	✓	✓	✓
Prescriptions	✓	✓	✓	✓
Inpatient care during hospitalisation				
Seclusion order		✓		
Restraint order		✓		
Electroconvulsive therapy^b^		✓		
Discharge plan or planning^a,b^		✓		
Therapies specific to hospitalisation^b,d^		✓		
Outpatient care during follow-up				
Outpatient service visit within 7 days of discharge from index admission			✓	
Regular outpatient service visits			✓	✓
Online medical examinations			✓	✓
Local social and welfare resources				
Number of social and welfare service agencies in the patient’s area of residence				✓

*EQ-5D-5L* EuroQol five dimensions and five levels, *PSP* Personal and Social Performance scale, *SDS-J* Sheehan Disability Scale—Japanese version

^a^Component of the READMIT index

^b^Possible responses are YES/NO

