In addition, study staff will collect data on assessment point-specific variables. At the time of admission (T1), information on sociodemographic characteristics (sex, age, living condition, pension, types of medical and social service utilization), diagnoses, existence of a crisis plan, and past prescriptions will be gathered. We will also assess current psychiatric statuses that are likely to affect self-reported measures at admission (T1), including hallucinatory paranoid state, psychomotor excitement, stupor, residual schizophrenia, depressive state, manic state, delirium, twilight state, and dementia symptoms. In addition, the READMIT items (e.g., comorbidities, past emergency service use; see Vigod et al.) will be included as the participants’ demographic and background information [17]. At the time of discharge (T2), information on the patients’ prescriptions and types of care provided during hospitalization will be collected. During follow-up assessments (T3 and T4), the outpatient services and prescriptions that participants received during the previous 6 months will be recorded. All information will primarily be gathered through medical records. If the medical records do not include an assessment item, trained staff members will ask the participants to provide additional data. In addition, we will collect data on the number of social or welfare service agencies in the patient’s living area as an environmental geographical variable using the electronic Regional Mental Health Resources Analyzing Database (ReMHRAD, https://remhrad.ncnp.go.jp/), which can identify the number of service agencies in the patient’s local government area of residence.

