#### Primary objectives

For the primary objective, mixed-effects logistic regression will be performed to assess the relationship between the QoL score at discharge (T2) and readmission over a 12-month follow-up period beginning at discharge after the index admission. In the first model, we will adjust for sex, age, and diagnosis. Next, we will conduct an analysis that adjusts for the potential covariates suggested in previous studies, for example, function (PSP score), symptoms, accommodation, problematic behaviors, past hospitalization, comorbidities, and utilization of outreach services after discharge, in addition to sex, age, and diagnosis. Statistical significance will be set at 5% (two-tailed). In these models, we will only include participants with data for both the primary exposure (QoL score at discharge, T2) and the primary outcome (readmission over 12 months).

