#### Secondary objectives

We will again conduct mixed-effects logistic regression to assess whether self-reported disability, empowerment/self-agency-related measure or service satisfaction with inpatient care at discharge (T2) affect readmission over a 12-month follow-up period beginning at discharge after the index admission, respectively. In addition, we will conduct an analysis that adjusts for the same potential covariates as the QoL analyses. We will only analyze patients with data on self-reported disability (T2), empowerment/self-agency-related measure (T2) or service satisfaction (T2) with inpatient care and readmission.

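### The fully adjusted readmission models name outreach use after discharge as a covariate; it arises after the exposure and overlaps the outcome window, so the adjusted QoL odds ratio is at risk of bias of unknown size and direction

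*Protocol article*

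**What the plan says.** Under Primary objectives, the protocol plans mixed-effects logistic regression of "readmission over a 12-month follow-up period beginning at discharge after the index admission" on the EQ-5D-5L score at discharge (T2). There are two models. For the first: "In the first model, we will adjust for sex, age, and diagnosis". The second adds covariates drawn from earlier studies. The list is introduced as examples: function, symptoms, accommodation, problematic behaviors, then "past hospitalization, comorbidities, and utilization of outreach services after discharge, in addition to sex, age, and diagnosis".

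Under Secondary objectives, the models for self-reported disability, empowerment/self-agency and service satisfaction get a further analysis that "adjusts for the same potential covariates as the QoL analyses".

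On measurement, the section on clinical, social and other measures says that at T3 and T4 "the outpatient services and prescriptions that participants received during the previous 6 months will be recorded". Table 1 has a separate row, "Case management or outreach services", ticked at T1, T2, T3 and T4. Under Procedures for data collection, the T3 and T4 assessment sheet also carries readmission.

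**The concern.** A covariate in a model for the association of discharge QoL with later readmission should be fixed by the time QoL is measured. Outreach after discharge is not. Three routes are open:

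- **Mediator.** Low QoL at discharge may lead to outreach being arranged, and outreach may change the risk of readmission. Adjusting then removes part of the association under study.
- **Consequence of the outcome.** A readmission may prompt outreach. If low QoL also prompts it, outreach is a common effect of exposure and outcome, and conditioning on it distorts the odds ratio.
- **Less opportunity.** A patient readmitted early has less time in the community in which to receive outreach.

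The protocol's own Background makes these links plausible. It says that QoL is likely to differ across post-discharge settings such as outreach, and it lists care after discharge and community care among the factors for readmission.

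The fully adjusted model carries weight. The Background asks whether patients' views are independent risk factors. The Discussion ties its recommendation for routine practice to prediction that survives adjustment for covariates. A model that needs information unavailable at discharge cannot support prediction from discharge.

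**Working it through.** **Timing.** The exposure is fixed at T2. The outcome runs from T2 to T4, 12 months. Use of outreach after discharge can be known only from T3 and T4. If the outreach row uses the same 6-month look-back that the text states for outpatient services, the two visits together cover T2 to T4, which is the outcome window. Nothing in the article confines the variable to outreach before a first readmission or to outreach arranged by discharge.

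**Inputs from the protocol.** Sample size consideration gives d = 0.26 and a readmission rate of 40%. With a normally distributed score of equal variance in the two groups, d = 0.26 corresponds to a log odds ratio of -0.26 per SD of QoL, so OR = exp(-0.26) = 0.77. The protocol gives no figure for outreach; every outreach strength below is an assumption.

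**Formula when outreach follows readmission.** Let x be QoL in SD units, Y readmission and O outreach, with logit P(O) = a + b·x + c·Y. By Bayes' rule, logit P(Y | x, O) equals logit P(Y | x) plus log[P(O | Y=1, x) / P(O | Y=0, x)]. The slope of the added term in x is b(p0 - p1), for O = 1 and O = 0 alike, where p0 and p1 are the outreach proportions without and with readmission at that x. Evaluated at average QoL:

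adjusted log OR ≈ -0.26 + b(p0 - p1)

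With b = ln 0.70 = -0.357 per SD (lower QoL, more outreach) and p0 = 0.15:

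| Outreach if readmitted (p1) | Shift b(p0 - p1) | Adjusted log OR | OR |
|---|---|---|---|
| 0.40 | +0.089 | -0.171 | 0.84 |
| 0.30 | +0.054 | -0.206 | 0.81 |
| 0.15 | 0 | -0.260 | 0.77 |
| 0.10 | -0.018 | -0.278 | 0.76 |
| 0.075 | -0.027 | -0.287 | 0.75 |

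Simulation with 1,000,000 patients per row agreed with these log odds ratios to within 0.006. If b = 0, the shift is zero whatever p1 is: a covariate that depends on readmission alone leaves the QoL odds ratio unchanged. A simulation with a readmission-to-outreach OR of 3 and b = 0 gave 0.77 before and after adjustment.

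**Stronger collider settings (simulated).**

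| Readmission-to-outreach OR | b per SD | Adjusted OR, true OR 0.77 | Adjusted OR, true OR 1.00 |
|---|---|---|---|
| 3 | -0.3 | 0.83 | 1.07 |
| 3 | -0.7 | 0.90 | 1.16 |
| 5 | -0.7 | 0.97 | 1.26 |

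**Outreach as mediator only (simulated).** With about 20% using outreach, b = ln 0.70 and an outreach-to-readmission OR of 0.5 to 0.6, the total log OR of -0.22 to -0.23 (OR about 0.80) becomes about -0.26 (OR 0.77) after adjustment. With b = -0.5 to -0.7 and an outreach-to-readmission OR of 0.5 to 0.4, a total OR of 0.82 to 0.85 becomes 0.77. Here adjustment moves the estimate away from the null.

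**The case against.** The strongest reply has four parts.

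- **The list is illustrative.** The covariates follow a phrase marking them as examples, and the exact definition of the outreach variable may sit in an analysis plan not shown here. That stands as a limit on certainty. But outreach after discharge is named outright, so this is a stated choice and not an omission.
- **The first model is clean.** It has no outreach term, both models will be reported, and a discrepancy would be visible. That stands too and narrows the point to the second primary model and its secondary counterparts. It does not make the second model interpretable.
- **Outreach after discharge may continue earlier outreach,** and so partly stand in for a factor present before discharge. True, but Table 1 already has the T1 and T2 values, which serve that purpose without the overlap.
- **The aim is exploratory.** The study sets out to explore an association, and the limitations say it cannot clarify the effect of an intervention. That lowers the stakes, but the independent-predictor claim remains.

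A reader might go further and infer that the QoL odds ratio is biased, that it is attenuated by 20-35%, and that power falls accordingly. The documents do not support this. That attenuation is the pair of scenarios with p1 of 0.30 and 0.40; no figure for outreach use is given, and the other mechanisms move the estimate the opposite way or not at all.

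**Conclusion.** The point holds as a specification fault in the second (fully adjusted) primary model and in the secondary models that share its covariates. The fully adjusted odds ratio is at risk of over-adjustment or collider bias and cannot be read plainly as the association of discharge QoL with later readmission.

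Direction depends on facts the protocol does not supply. If outreach follows readmission but does not depend on QoL given readmission, there is no bias. If low QoL and readmission both raise outreach, the estimate moves toward or past the null, and a true null can appear as 1.05 to 1.26 (the low end is exp(0.054), from p1 = 0.30 above). If outreach mediates a protective effect, or early readmission leaves less time for it, the estimate moves away from the null. Across the assumed settings in which outreach follows readmission, a true 0.77 became anything from 0.75 to 0.97. That range illustrates sensitivity; it is not an estimate.

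The conclusion rests on two readings: that T3 and T4 fall 6 and 12 months after discharge, as under Study design and settings, and that the outreach row there records use since the last assessment. The look-back sentence itself names outpatient services and prescriptions, not outreach.

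**What to change.** In the fully adjusted primary and secondary readmission models:

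1. State that every covariate takes its value at or before discharge. This matters also for function, symptoms and problematic behaviors, which Table 1 collects at all four time points.
2. Replace outreach use after discharge with the case-management/outreach item recorded at T1 and T2. Table 1 places that row under past utilisation, so confirm what the T2 entry captures.
3. Report any model that includes post-discharge outreach only as a labelled sensitivity or descriptive analysis. A time-varying version, counting outreach only before the first readmission, is possible only if the dates of outreach and readmission are available; the article does not show that they are collected.

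The cost is a sentence or two in the analysis section and no new data for items 1 and 2. The small downside is that the main adjusted model no longer accounts for differences in outreach that begin after discharge.

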### Sample size consideration

Based on the primary aim of this study, the sample size was calculated using the effect size reported by a previous study. That study reported an association between readmission and QoL scores (*d* = 0.26) [20] and indicated the readmission rate in Japanese psychiatric hospitals (40%, ratio of approximately 1 vs 1.5) [38]. In addition, the calculation was based on a power of 70% at a two-sided significance level of 5%. Based on these values, 430 participants will be needed. Assuming that 20% of the participants will not be discharged within 12 months and a 25% attrition rate [57], the final number of participants required was estimated to be 624. This calculation was conducted using Stata version 15.

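### The primary analysis is restricted to patients with 12-month readmission data and does not say how patients lost earlier are classified; either reading loses information or selects on the outcome

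*Protocol article*

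**What the plan says.** Under Data analysis, Primary objectives, the protocol article states that "mixed-effects logistic regression will be performed to assess the relationship between the QoL score at discharge (T2) and readmission over a 12-month follow-up period". The outcome is therefore yes or no over a fixed window, with no time at risk. The same section fixes the analysis set: "we will only include participants with data for both the primary exposure (QoL score at discharge, T2) and the primary outcome". Secondary objectives applies a matching restriction to the disability, empowerment and satisfaction analyses.

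Sample size consideration plans for losses: "Assuming that 20% of the participants will not be discharged within 12 months and a 25% attrition rate". It does not divide the 25% between missing questionnaires and unknown readmission status.

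Procedures for data collection has staff record readmission at both the 6-month (T3) and 12-month (T4) assessments. The section on clinical, social and other measures gives medical records and participant interviews as the sources. Some patients who are not followed to 12 months will therefore have known status for part of the year. Additional objectives uses partial follow-up for the repeated patient-reported outcomes, on the ground that mixed models tolerate missing data. The article describes no counterpart for the primary outcome.

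**The concern.** The requirement to have primary outcome data can be read in two ways for a patient lost before 12 months.

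- **Reading A: a complete 12-month record is required.** Everyone lost early is excluded. A patient readmitted in month 3 and lost in month 8 goes out although the outcome is already known to be yes. A patient followed free of readmission for nine months also contributes nothing.
- **Reading B: a known readmission counts as outcome data.** The first patient stays and the second goes. Inclusion then depends on the outcome.

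Reading A costs events and power in a study planned at only 70% power. Reading B inflates the readmission proportion and can distort the QoL odds ratio. Leaving the choice open also allows it to be made after the data are seen, between two sets with different event rates.

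**Working it through.** **Inputs from the protocol (Sample size consideration):** d = 0.26; 40% readmission, ratio about 1 to 1.5; two-sided 5%; 70% power; 430 evaluable; 624 to recruit; 20% not discharged; 25% attrition.

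**Assumptions of this check:** all discharged patients have a T2 QoL score; readmission and dropout have constant hazards; dropout is independent of readmission; the 25% applies to discharged patients and is entirely loss of readmission status. The last is an upper case and is varied in step 4.

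**1. The plan's own figure.** The smaller group is (1 + 1/1.5) × (z₀.₉₇₅ + z_power)² / d².
- 70% power: 1.667 × (1.960 + 0.524)² / 0.0676 = 152.2, so 153 + 230 = 383, not 430.
- 75% power: 1.667 × (1.960 + 0.674)² / 0.0676 = 171.1, so 172 + 258 = 430.
- 624 agrees with 430 × 1.45 = 623.5.

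This mismatch is a separate matter. Only 624 is carried forward: 624 × 0.80 = 499 discharged.

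**2. Who is lost.** Hazards per year: readmission λ = −ln 0.60 = 0.511; dropout μ = −ln 0.75 = 0.288.
- Followed to 12 months without readmission: 0.60 × 0.75 = 0.450.
- Readmission observed before any dropout: λ/(λ+μ) × (1 − 0.450) = 0.640 × 0.550 = 0.352, or about 176 patients.
- Dropout with no readmission seen: 0.360 × 0.550 = 0.198, about 99 patients.
- Dropout after a readmission: 0.250 − 0.198 = 0.052, about 26 patients.

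**3. The two readings at 25% loss.**

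| Handling | Analysed | Readmissions | Apparent proportion |
|---|---|---|---|
| A: exclude all lost | 499 × 0.75 = 374 | 374 × 0.40 = 150 | 40% |
| B: keep lost patients with known readmission | 499 × (0.352 + 0.450) = 400 | 176 | 0.352/0.802 = 44% |
| Censor at last contact | 499 | 176 | not applicable |

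Reading A discards 26 of 176 observed readmissions, or 15%.

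**4. If fewer patients lose readmission status (same formulas).**

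| Status lost | A: analysed | Observed readmissions discarded under A | B: apparent proportion |
|---|---|---|---|
| 5% | 474 | 5 of 195 | 40.7% |
| 10% | 449 | 11 of 190 | 41.4% |
| 15% | 424 | 16 of 186 | 42.2% |
| 25% | 374 | 26 of 176 | 43.9% |

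**5. Power at 25% loss.** By formula, reading A gives Φ(0.26 × √(374 × 0.4 × 0.6) − 1.96) = 69%. Two separate simulations, each of 1,500 studies of 499 patients with no covariates or hospital effect, gave:
- log hazard ratio −0.205 per SD of QoL (d about 0.26): 67% under A, 72% under B, 77% with a censored Cox model, 80% if all 499 were followed fully;
- log hazard ratio −0.21: 70% under A, 78% with Cox.

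**6. Bias in the QoL log odds ratio per SD (large simulated samples, true value about −0.265).**

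| Dropout log-hazard slope per SD of QoL | Reading A | Reading B |
|---|---|---|
| 0 | −0.264 | −0.265 |
| −0.3 | −0.265 | −0.319 |
| −0.6 | −0.263 | −0.378 |
| +0.3 | −0.268 | −0.220 |
| +0.6 | −0.265 | −0.163 |

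The slopes are assumed; the protocol gives none. Reading A is unbiased here because dropout depends only on QoL, which is in the model.

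**The case against.** The strongest reply is that the 25% is a planning figure for attrition in general. Readmission comes largely from medical records, patients treated outside the participating hospitals and their affiliates are not eligible, and inpatient, outpatient and outreach staff share information to limit loss. Many patients who stop returning questionnaires may still have known readmission status. If part of the 25% is missing T2 scores, a time-to-event model does not recover those patients. This stands, and it makes the 25% figures an upper case.

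Recruitment is also already inflated for attrition, and a logistic model over a fixed window matches the stated objective. Both are true. Inflation pays for lost patients, however; it does not justify discarding what was observed on them, and it does not settle who is in the analysis.

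Table 1 lists number, length and type of admissions but no readmission date or last-contact date, so timing cannot be taken as already available. This also stands and is reflected in the fix.

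A reader might infer that the plan treats lost patients with and without a readmission unequally, and at the same time discards follow-up on a full 25%. The text does not support that. Unequal handling follows only under reading B, where about 5 of the 25 points are kept. Loss of all 25 points follows only under reading A, where everyone lost is handled alike. Nor do the documents support a claim that the QoL association will be biased in a given direction.

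**Conclusion.** The concern holds in this form: the protocol fixes an outcome-complete analysis set for its primary model without defining outcome data for patients lost before 12 months, and each reading has a cost. Under A, at the upper case of 25% loss, about 15% of observed readmissions are discarded and power is some 8 to 10 points below that of a censored analysis. Under B, the readmission proportion is overstated by about 4 points, and the QoL odds ratio is too strong or too weak according to how dropout relates to QoL; if they are unrelated, the simulation shows no bias. At 10% loss the corresponding figures are about 6% of readmissions discarded (11 of 190) and an overstatement of 1.4 points.

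The sizes rest on constant hazards, independent dropout and models without hospital effects or covariates. The ambiguity in the rule rests on none of these. The restriction is written into the article, so it is not a detail left to an analysis plan. It should be corrected, but it does not invalidate the design.

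**What to change.** 1. State one classification rule, before the data are analysed, for patients lost before 12 months with and without an earlier readmission. Apply it to the primary and secondary readmission analyses.
2. Include every discharged patient with a T2 QoL score and analyse time from discharge to first readmission. Use a Cox model or, if dates are not captured, a discrete-time model on the T3 and T4 intervals, with a hospital random effect and the covariates already planned. Censor at last known contact or 12 months.
3. Report this as the primary analysis, or as a pre-specified analysis beside the 12-month logistic model.

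The cost is a change of wording and the recording of readmission and last-contact dates from records that staff already review. The Cox model yields a hazard ratio beside the odds ratio and adds proportional-hazards and independent-censoring assumptions. The discrete-time version uses less of the partial follow-up; its power was not calculated. Imputing missing T2 QoL scores and treating death as a competing event are optional refinements and not part of this point.
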